## Study Procedures

## Randomization and blinding

Participants will be randomized through REDCap using stratified assignment based on biological sex and age (65-72 and 73+) to maintain equal representation of older vs. younger males and females in each group. Once randomized, patients will be informed of their assigned condition, and their study visits will be scheduled. Both participants and the research staff who conduct the assessments will not be blinded to the participants’ treatment assignments. Secondary coders that review videos weekly to assess quality and for safety control will be blinded.

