**Methods**

**Participants**

Eligible participants will be identified through mailing recruitment letters to Penn State Health patients ≥ 65 years of age meeting eligibility criteria and residing in zip codes within a 30-mile radius of Penn State Health-Milton S. Hershey Medical Center.

Eligibility screening process

Screening for eligibility will occur prior to the signing of the informed consent document. Interested participants will be screened by phone by research staff who will read a phone screening document which will ensure eligibility and inform them of study procedures.

During screening, the items from the Physical Activity Readiness Questionnaire (PAR-Q; attached) will be asked. The participant answers will be transferred to the permission slip (attached) by research staff and will be faxed to the Primary Care Provider (PCP) of the participant for the PCP to review and provide permission.

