**Exclusion Criteria**

1. Chest pain or a heart condition on the PAR-Q
2. Planning to have surgery in the next 3 months
3. Cognitive impairment
4. Unable to exercise
5. Being currently physically active

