## Delayed intervention control

Participants assigned to the delayed intervention control group will continue care as usual. Following the completion of the 12-week follow-up, participants in the delayed group will begin 12 weeks of physical activity intervention with a one-on-one audio-video Zoom coaching session occurring during the initial first week. At that time, the information given to the physical activity treatment intervention group regarding the daily exercise will be given to the delayed group.

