## Sample size determination

Effect size calculations are based on evidence that 30 second chair stand performance declines with age and predicts future functional decline. We considered a large effect size as healthier patients in our pilot showed large gains (i.e., *d > 1.00)* in squat performance, but because our intended sample has at least some degree of limitations with walking, we expect a more conservative effect of the intervention on measures of physical function (i.e., d = .60).

Based on a 2-group design (intervention, control) assuming a moderate standardized between-group difference at 12 weeks (Cohen’s d = .60), a sample size of 88 (44 per group) would be needed to detect a difference between groups with a two-sided significance level of 0.05 and 80% power. To account for an anticipated 20% attrition rate over the study period, we will recruit up to 110 participants.

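### Nothing stops two members of one household from enrolling and being allocated to different arms, so a control may live with a participant doing the programme, which could dilute the 12-week contrast

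*Protocol*

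**What the plan says.** Recruitment (Protocol, Participants): "Eligible participants will be identified through mailing recruitment letters to Penn State Health patients" aged 65 or over who live within 30 miles of one medical centre. Two people at one address can therefore both be invited.

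Eligibility (Protocol, Inclusion Criteria and Exclusion Criteria): six inclusion and five exclusion criteria, the last being "Being currently physically active". None concerns a cohabiting participant.

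Allocation (Protocol, Randomization and blinding): "Participants will be randomized through REDCap using stratified assignment based on biological sex and age (65-72 and 73" and over). The unit is the individual, and participants are told their arm.

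Intervention (Protocol, Intervention; Coaching; Self-monitoring, feedback, and messaging): a daily workout of about four minutes done at home, with morning emails linking to exercise videos and Zoom coaching at baseline and weeks 2, 4 and 8.

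Control (Protocol, Delayed intervention control): these participants "will continue care as usual" and start the programme after the 12-week follow-up.

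Sample size (Protocol, Sample size determination): "we expect a more conservative effect of the intervention on measures of physical function (i.e., d = .60"); "a sample size of 88 (44 per group) would be needed" for a "two-sided significance level of 0.05 and 80% power". Then: "To account for an anticipated 20% attrition rate over the study period, we will recruit up to 110 participants".

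**The concern.** The comparison needs controls who do not take up the programme for 12 weeks. A control whose partner is in the intervention arm is poorly placed for that. The workout takes place in the same home every day, is short, and is coached on a video call that the control may overhear. Two of its four exercises, push-ups and chair stands, need nothing that most homes lack. The control has also volunteered for the programme and been told to wait.

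Stratifying by sex makes this more than a remote possibility for mixed-sex couples. The partners can never share a stratum, so nothing links their two allocations.

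Any benefit that an exposed control gains makes the estimated effect smaller than the true one. The sample size includes a margin for attrition but none for dilution, so any dilution takes power below the stated target.

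**Working it through.** **Inputs from the protocol (Sample size determination).** d = 0.60, two-sided alpha 0.05, 80% power, 44 per group, 20% attrition, up to 110 recruited. Equal group sizes imply 1:1 allocation.

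**Assumptions, not in the protocol.**
- h: share of participants who enrol together with another member of their household, taken as 5%, 10% and 20%, and the same among those analysed as among those recruited.
- s: share of the full effect that an exposed control gains, taken as 0.5 (half uptake) and 1 (full uptake).
- The standard deviation does not change.

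**Step 1: reproduce the plan's figures.** Normal approximation: n per group = 2 × (1.960 + 0.842)² / 0.60² = 43.6, rounded up to 44, so 88 in total. Attrition: 88 / 0.80 = 110. Both agree with the protocol. Power at 44 per group is 80.4% by the normal approximation and 79.5% by the t-test. The t-test figure is the reference below.

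**Step 2: exposed controls.** With 110 participants there are 110 × h / 2 couples. Under independent 1:1 allocation, a couple is split with probability 1/2, and each split couple contributes one exposed control. The expected number is 110 × h / 4 out of 55 controls, a share of h / 2.
- h = 5%: 2.75 couples, 1.375 exposed controls, 2.5% of controls.
- h = 10%: 5.5 couples, 2.75 exposed controls, 5% of controls.
- h = 20%: 11 couples, 5.5 exposed controls, 10% of controls.

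**Step 3: diluted effect and power.** d_eff = 0.60 × (1 − (h / 2) × s), with power from a two-sided t-test at 44 per group.

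| h | s | d_eff | Power |
| --- | --- | --- | --- |
| 0 | – | 0.600 | 79.5% |
| 5% | 0.5 | 0.593 | 78.5% |
| 5% | 1 | 0.585 | 77.4% |
| 10% | 0.5 | 0.585 | 77.4% |
| 10% | 1 | 0.570 | 75.3% |
| 20% | 0.5 | 0.570 | 75.3% |
| 20% | 1 | 0.540 | 70.7% |

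For example, h = 10% and s = 1 gives 0.60 × (1 − 0.05) = 0.57.

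**Step 4: the extreme.** If h = 20% and by chance all 11 couples were split, 11 / 55 = 20% of controls would be exposed. With full uptake, d_eff = 0.60 × 0.80 = 0.48 and power is 60.5%. This is a bound, not an expectation.

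**The case against.** The strongest reply is that individual stratified randomisation is ordinary and that nothing in the protocol suggests couples will be common. Both partners would have to be 65 or over, have difficulty walking, be inactive, be patients of the same health system, pass the PAR-Q cardiac items and have their provider's permission. An exposed control would also receive no coaching, goals, daily prompts or performance feedback of their own, so full uptake is unlikely. This stands. It means that the loss is conditional and favours the milder rows of the table.

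Some stronger readings are tempting, but the document does not support them:
- *That the contrast will shrink.* The protocol gives no number of couples and no uptake, so only a possibility is shown.
- *That households cannot be identified because they are not recorded.* The protocol does not say so. Letters are mailed to patients selected by zip code, so addresses must be held, and shared homes could probably be found for a sensitivity analysis. Finding them would still not recover what an exposed control's outcome would have been without exposure.
- *That the equipment at home is what exposes the control.* The Intervention section gives bands and stepper to participants before the baseline visit without naming an arm, so controls may hold their own. What is specific to a split couple is the partner's workout and coaching.
- *That correlation between partners undermines the analysis.* Under independent allocation, same-arm pairs raise the variance of the contrast and split pairs lower it. With about half of each, the two roughly offset.
- *That the sample size is miscalculated.* It reproduces on its own inputs.

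**Conclusion.** The point holds in a limited form. The eligibility and randomisation rules allow cohabiting participants, a male-female couple is split about half the time, and a control in a split couple can see and copy the programme throughout the comparison. Any resulting bias is toward zero.

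Its size rests wholly on the assumed h and s. Against 79.5%, the loss of power is about 1 to 2 percentage points with 5% in couples, 2 to 4 with 10%, and 4 to 9 with 20%, from half to full uptake. If couples are few, the effect is negligible. The case for acting is that the safeguard is very cheap and that contamination cannot be undone once it has happened. Priority: consider.

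**What to change.** Add one participant per household to the eligibility criteria and check it with one question at the existing phone screen. If a second member of the household is interested, offer that person the programme outside the trial after the first member's week 12.

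This removes exposure through a co-enrolled partner and leaves the planned 88 evaluable and 110 recruited unchanged. The cost is one protocol line, one screening question and the few otherwise eligible people who cannot be randomised.

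Allocating household members together would also prevent split couples, but it is not recommended. It creates clustering that the sample size would have to cover: with 10% of participants in couples and an assumed household correlation of 0.1 to 0.3, the design effect 1 + h × ICC is 1.01 to 1.03. Evaluable numbers rise to 89 (88 × 1.01 = 88.9) to 91 (88 × 1.03 = 90.6), and recruitment to 112 (89 / 0.8 = 111.3) to 114 (91 / 0.8 = 113.8), above the planned 110.

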**Intervention**

FAST-2 will be a two-group, 12-week, delayed-treatment randomized trial.

Participants will be provided with a set of four resistance bands with handles (10-40 pounds of resistance) and a standard aerobics stepper that can be adjusted to 4, 6, or 8 inches in height prior to the baseline visit. They will be instructed to perform four exercises daily, each lasting 30 seconds, and to perform as many repetitions as possible during those 30 seconds. Thirty seconds of rest will be allowed in between the exercises. Each day participants will be asked to perform push-ups, chair stands, two-arm rows, and stair stepping in the same order during each session. No written instructions will be provided, although links to videos of each exercise will be included in email communications. Participants will be instructed to perform the exercises all seven days of the week. Modifications will be provided based on the participants’ functional level and form.

Push-ups can be modified in any of the following ways: by resting on the knees instead of the toes, by placing the hands on the kitchen countertop (30 inches in most homes), by placing the hands on a set of steps (starting with the 4^th^ step from the floor) or by placing the hands on the wall. When participants are able to perform 15 repetitions of push-ups using one of the modified methods, they will beasked to progress to a higher level of difficulty (e.g., place the hands on the 3^rd^ step from the floor).

Chair stands will be performed, by default, by placing the arms across the chest, but participants can modify them if needed by placing two hands on the knees, one hand on a knee or with arms not placed across the chest. Participants will be instructed to use a standard chair with arms, without wheels and with a seat height of approximately 17 inches regardless of the height of the subject. Participants will be encouraged to progress, as they are able to do so safely, to the default position of placing their arms across the chest.

Two-arm seated band rows will be performed with the resistance band looped around the arches of the feet to allow for a full range of motion. Participants will be instructed to pull their elbows back to touch the body to complete a repetition while squeezing the shoulder blades behind together.

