### Coaching

At baseline and at weeks 2, 4 and 8, each participant will complete a one-on-one Zoom audio-video coaching session led by a research staff member with expertise in exercise and health psychology with the goal of improving each participant’s personal performance records. Each coaching session will last 10-20 minutes, depending on the participants’ instructional needs. The coach will begin each session by asking the participant a question designed to build rapport (i.e., “small talk”). Next, the coach will review the self-reported adherence and performance data of participants, congratulating them on any personal records and positive performance trends. The coach will emphasize to the participants the importance of moving as rapidly as possible (without sacrificing form) to pursue a standardized goal of increasing chair stands and stair steps, by four and two repetitions, respectively over the course of the 12-week intervention. The same goal will be communicated by the coach to all participants. The stated rationale of this goal is to improve walking ability, as all participants have reported difficulty walking at baseline. Before beginning the exercises, the participants will orient their camera so that the entire body will be visible by the coach. During each session, the coach will passively observe the participant complete the entire workout. The coach will ask each participant to complete the workout normally, as if they are not being observed. Upon completing the 4-minute exercise session, the coaches will provide feedback and correction (if necessary) relating to exercise form. Where form correction is necessary, the coach will demonstrate the proper movement and confirm understanding by viewing the participant perform the corrected exercise. Modifications and progression methods will be suggested and discussed. For example, once a participant can complete 15 push-ups with their hands on a kitchen countertop, the coach will encourage the participant to progress to push-ups with their hands on the 4^th^ step of a staircase (if available in the home of the participant). Safety will be emphasized during each session; coaches will encourage participants to place the stepper in a corner (to allow them to regain their balance, if needed) and to do chair stands on a carpeted floor, so the chairs will not slide. The coach will end each session by answering any questions.

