**Measures**

**Primary Outcome Measures**

**Functional Performance Measures**

The participants in both groups will complete three functional performance measures while being observed by a trained researcher over Zoom at baseline, week 6 and week 12 (The Five-Times Sit-to-Stand (FTSTS) test, part of the Short Performance Physical Battery(SPPB)), the One-Legged Stance Test (OLST) and the 30 second chair stand test. As with the coaching sessions, the participants will orient their camera so that the entire body will be visible to the researcher

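### As written, participants learn their arm before the baseline functional tests, so baseline effort can differ by arm and bias the Group x Time estimates for the three functional outcomes

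*Protocol*

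**What the plan says.** **Order of steps.** Protocol, Randomization and blinding: "Once randomized, patients will be informed of their assigned condition, and their study visits will be scheduled". The sentence does not name the baseline visit. On blinding, the same section says: "Both participants and the research staff who conduct the assessments will not be blinded".

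**Contact before randomisation.** Protocol, Participants (eligibility screening): "Interested participants will be screened by phone by research staff". Provider permission follows, and written consent is required under Ethics Approval and Informed Consent. No physical test is described at this stage.

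**Baseline visit.** Protocol, Functional Performance Measures: both groups do "three functional performance measures while being observed by a trained researcher over Zoom at baseline, week 6 and week 12". Protocol, Intervention, has the bands and stepper supplied ahead of that visit ("adjusted to 4, 6, or 8 inches in height prior to the baseline visit"). Protocol, Coaching: "At baseline and at weeks 2, 4 and 8, each participant will complete a one-on-one Zoom audio-video coaching session". The delayed group has its first coaching session only after its 12-week follow-up (Delayed intervention control).

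**Scoring.** Protocol, Daily exercise performance: timed tests are recorded live and re-rated offline by a blinded reviewer. For differences above one second the blinded time replaces the live one; for differences under one second the two are averaged. Disagreements on repetition counts go to the blinded rater.

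**Analysis.** Protocol, Statistical analysis: linear mixed-effects models for change over 12 weeks and the Group x Time interaction, by intention to treat, with the mixed model relied on for missing data.

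**The concern.** All three functional tests depend on effort: the FTSTS is done as fast as the participant can manage, the OLST as a held stance, and the 30-second test as a maximal repetition count. If the arm is known when the first test is done, the baseline is no longer a pre-allocation measurement. Participants may try more or less hard, and the live assessor may encourage more or less, according to arm.

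The primary analysis is of change by group, so a baseline difference caused by knowing the arm counts as treatment effect with its sign reversed. A lower intervention-arm baseline favours the intervention; a higher one works against it. No later analysis can recover an uncontaminated baseline, so the protocol itself has to settle the order.

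A second consequence concerns intention to treat. Someone who withdraws on learning the assignment, before the baseline visit, contributes no outcome value at all, and the mixed model has nothing to use for that person.

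**Working it through.** **1. Reconstructing the order**

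| Step | Where in the protocol | What it implies |
|---|---|---|
| Phone screen, provider permission, consent | Participants; Ethics Approval and Informed Consent | No functional test described |
| Randomisation and disclosure, then scheduling of visits | Randomization and blinding | Arm known by the time visits are arranged |
| Equipment supplied | Intervention | Before baseline; timing relative to randomisation not given |
| Baseline tests | Functional Performance Measures | Done at a Zoom visit, both groups |
| First coaching session | Coaching; Delayed intervention control | At baseline for the intervention arm only, so the arm is known by then |

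No section puts the baseline tests before randomisation or withholds the arm until they are done.

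**2. The plan's own figure**

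Inputs from Sample size determination: d = 0.60, two-sided alpha 0.05, power 80%, attrition 20%.

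- n per arm = 2(1.960 + 0.842)² / 0.60² = 43.6, rounded up to 44, so 88 in total.
- 88 / (1 − 0.20) = 110.

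Both stated numbers are reproduced. The point does not change them.

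**3. How a baseline shift enters the estimate**

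Let b be the amount, in SD units, by which knowing the arm lowers the intervention-arm baseline relative to control. With time as a category and complete data, the baseline-to-week-12 Group x Time contrast is the difference between arms in mean change, so its bias is b.

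With equal SDs (set to 1) and correlation rho between baseline and week 12:

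- SE of the contrast = √[2(1 − rho) × 2/44]
- rho = 0.5: SE = √(2/44) = 0.213
- rho = 0.7: SE = √(1.2/44) = 0.165

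**4. Type I error with no true effect**

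The documents give neither b nor rho; both are assumptions. Two-sided test at 0.05, noncentral t, 86 df, noncentrality b/SE:

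| b (SD) | b / 0.60 | Type I error, rho 0.5 | Type I error, rho 0.7 |
|---|---|---|---|
| 0 | 0% | 5.0% | 5.0% |
| 0.10 | 17% | 7.5% | 9.2% |
| 0.20 | 33% | 15.3% | 22.4% |
| 0.25 | 42% | 21.3% | 32.2% |

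A shift of the opposite sign gives the same two-sided error with no true effect. With a true benefit it would hide part of it.

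**5. Would baseline adjustment rescue it?**

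The protocol does not specify such adjustment. If it were used, the bias would be rho × b with SE √[(1 − rho²) × 2/44]. At rho = 0.5 and b = 0.20 the bias is 0.10, the SE 0.185 and the type I error 8.4% (normal approximation): smaller, but not removed.

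**6. With baseline tested before disclosure**

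b from this source is 0, and it adds nothing to the 5%.

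**The case against.** **The order is inferred.** The randomization section speaks only of study visits, and equipment timing is given relative to baseline, not to randomisation. That is fair: the sequence is pieced together from several sections. But every relevant section fits it, none contradicts it, and staff following the text would test after disclosure.

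**Blinded re-rating protects the data.** It largely does for scoring, and baseline is not exempt from it. Two gaps remain. Timing differences under one second are averaged, so the unblinded reading keeps half its weight. And a rater of a recording sees only the performance given, so effort and encouragement are untouched.

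**The magnitude is assumed.** This stands. The figures illustrate sensitivity and do not estimate the bias. Participants and live assessors also know the arm at weeks 6 and 12, so the calculation isolates baseline and says nothing about net bias.

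Four stronger readings are tempting but not supported:

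- *All Group x Time estimates are affected.* The fourth primary endpoint, daily exercise performance, has no pre-treatment baseline described, so this mechanism does not reach it.
- *The bias favours the intervention.* Reduced effort at baseline would, but practice before baseline would raise that baseline and work the other way. The net direction is unknown.
- *Early equipment gives a direct rehearsal of the tests.* None of the three test descriptions uses the bands or the stepper.
- *Controls hold the equipment for 12 weeks and are contaminated.* The supply sentence stands under Intervention, and the delayed group continues usual care and receives the exercise information only after week 12. The text leaves the recipients unclear; it does not show contamination.

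**Conclusion.** The concern holds for FTSTS, OLST and the 30-second chair stand. Followed as written, the protocol leads to baseline tests done after participants and live assessors know the arm. The Group x Time estimates for these outcomes can then be biased by an unknown amount in an unknown direction. The blinded re-rating narrows the route to effort, encouragement and part of the sub-second timing differences.

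Under an assumed baseline shift of 0.10 to 0.25 SD, 44 per arm and correlation 0.5, type I error would be about 7.5% to 21%, and the shift would equal 17% to 42% of the planned d = 0.60. A higher correlation makes the error larger. This rests on the inferred order, equal SDs, complete data and time treated as a category.

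Loss on disclosure is a further risk to intention to treat. The protocol gives no figure for it, and none is claimed here.

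**What to change.** **Randomization and blinding:** state the order explicitly as consent, then baseline functional tests completed and recorded, then REDCap randomisation and disclosure. If randomisation has to come first, withhold the arm from participants and live assessors until the baseline tests are done and recorded.

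**Intervention:** state which arm receives the bands and stepper, and when relative to the baseline tests and to randomisation.

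**Cost:** wording and scheduling, with the sample size unchanged at 88 analysed and up to 110 recruited. The first coaching session may need its own 10 to 20 minute call. Separating baseline testing from the start of exercise opens a gap, so the start of the 12-week clock, and with it weeks 6 and 12, must be defined the same way in both arms.

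This secures the baseline only. Effort bias from knowing the arm at weeks 6 and 12 remains and should be acknowledged as a limitation.
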